## Abstract

**Background:**

Cardiovascular disease (CVD) is the leading cause of early death worldwide, responsible for an estimated 29% of all global deaths. Reducing salt intake lowers blood pressure and risk of secondary cardiac events. However, identifying low salt foods can be challenging. SaltSwitch is a simple smartphone application (app) that enables shoppers to scan the barcode of packaged foods and receive an immediate, interpretive, traffic light nutrition label on the screen, along with suggestions for healthier lower-salt alternatives. A growing body of evidence suggests mobile technologies can support healthy behaviour change. However, robust evidence for the impact of smartphone interventions is lacking. This manuscript outlines the rationale and methods for a randomized controlled trial designed to determine the effectiveness of SaltSwitch in supporting people with CVD to make lower-salt food choices.

**Design/Methods:**

A 6-week, two-arm, parallel, randomized controlled trial is being undertaken in New Zealand (2 weeks baseline and 4 weeks intervention). Three hundred adults aged 40 years and older with CVD and their main household shoppers are recruited from research lists, cardiac rehabilitation clinics, and communities in Auckland. Participants are randomized to receive either the SaltSwitch smartphone app or no intervention (control). Randomisation is stratified by ethnicity and age. The primary outcome is the salt content of household food purchases. Secondary outcomes are the saturated fat and energy content of household food purchases, household food expenditure, use and acceptability of the SaltSwitch app by shoppers, and urinary sodium and blood pressure of participants with CVD. Ambulatory blood pressure and potential longer-term impact (12 weeks) of SaltSwitch will be assessed in sub-studies (n ~ 40 and n ~ 20, respectively). Household purchases of salt and other nutrients will be assessed using till receipt data electronically linked with branded food composition data.

**Discussion:**

The results of the SaltSwitch trial will determine the effectiveness, use and acceptability of a smartphone application to support lower salt food choices and secondary prevention of CVD.

**Trial registration:**

ACTRN12614000206628. Registered 30 March 2014.

## Background

Cardiovascular disease (CVD) is the leading cause of early death worldwide, being responsible for an estimated 15.6 million or 30% of all global deaths in 2010 [1]. In 2010, the number of years of life lost (YLLs) due to CVD and circulatory diseases was more than 273 million globally [1]; in New Zealand, CVD accounted for 17.5% (~167,000) of annual disability adjust life years, and Māori (indigenous New Zealanders) and Pacific peoples, and those living in lower socio-economic areas were disproportionately affected [2].

Secondary prevention is a vital strategy to reducing the global and national CVD burden, as 60% of hospitalisations occur in people who have been admitted for CVD in the past five years [3]. For people with CVD, adherence to a heart healthy diet has benefits additive to drug therapy and is associated with a reduction in mortality of between 8 and 45% [4–7]. Salt reduction is a key component of a heart healthy diet yet global and national salt intakes, particularly in high income countries, are far above recommended guidelines [8]. In New Zealand, population salt intake is ~9 g/day [9], almost twice the 2012 WHO recommendation and the recommended upper level of intake in NZ (5 g/day) [10, 11].

Cardiac rehabilitation programmes that offer dietary advice to people with CVD are provided by hospitals and non-government organisations in many countries, including New Zealand. However, they are resource intensive and uptake is generally low, largely due to access issues [12]. Furthermore, many people with CVD find it difficult to identify low salt food choices because nutrition labeling is confusing [13]. Smartphone technology may offer a more accessible, cost effective way of delivering nutrition interventions to cardiac patients. In New Zealand approximately two-thirds of the adult population owns a smartphone [14], and ownership is similar by ethnicity and income [15, 16]. Moreover, thousands of health and wellness applications (apps) are available direct to the public. Therefore, it is likely that smartphones will become synonymous with the future of patient self-care [17, 18].

SaltSwitch is a feature of the FoodSwitch smartphone app currently available in Australia, New Zealand, and the United Kingdom, designed to help consumers make healthier food choices [19]. FoodSwitch and SaltSwitch enable users to scan the barcode of packaged foods and receive an immediate interpretive, traffic light nutrition label on screen, along with a list of healthier lower-salt alternatives to ‘switch’ to (Figure 1). The main difference between FoodSwitch and SaltSwitch is an additional criterion in the algorithm used to determine healthier options [20]. The generic FoodSwitch algorithm allocates foods with a score based on their overall nutritional profile, and the additional criterion for SaltSwitch ensures that healthier alternatives are always lower in salt than the product scanned. SaltSwitch is not yet available in New Zealand, but it is available in the UK and Australia where it has proven functionality and consumer acceptability [21].

**Figure 1 Fig1:**
[figure not shown]
**The SaltSwitch smartphone application.**

A growing body of evidence indicates that mobile technology can support behaviour change [22], yet robust evidence for smartphone interventions is lacking. This manuscript outlines the rationale and methods for a randomized controlled trial designed to determine the effectiveness of SaltSwitch in supporting people with CVD to make lower-salt food choices. The primary hypothesis is that four weeks’ intervention with SaltSwitch will reduce the salt content of household food purchases compared with control. Secondary hypotheses are that four weeks’ intervention with SaltSwitch will reduce the saturated fat and energy content of household food purchases, and the systolic blood pressure and salt intakes (measured by urinary sodium excretion) of participants with CVD. The SPIRIT checklist for Standardised Protocol Items was followed in writing this manuscript [23] and the protocol described reflects the most recent version (Version 2 dated 12^th^ May 2014).

## Methods/Design

### Trial design

This study is a six-week, two-arm, parallel, randomized controlled trial (two weeks baseline and four weeks intervention; Figure 2) with a superiority design.

**Figure 2 Fig2:**
[figure not shown]
**SaltSwitch trial design.**

### Aims

The primary aim is to determine the effect of the SaltSwitch smartphone app on the salt content of food purchases made by households where at least one member has diagnosed CVD. Secondary aims are to evaluate the effect of SaltSwitch on: (1) saturated fat and (2) energy content of food purchases made by households; and (3) systolic blood pressure and (4) urinary sodium of participants with CVD. Household food expenditure, and use and acceptability of the SaltSwitch app by shoppers will also be assessed. Ambulatory blood pressure of participants with CVD and potential longer-term impact (12 weeks) of SaltSwitch will be assessed in two sub-studies (n ~ 40 and n ~ 20, respectively).

### Participants

Trial participants include individuals with CVD who complete most of the grocery shopping for their household, and pairs of individuals, one with CVD and the other who completes most of the grocery shopping. Only one person with CVD from each household may take part. Participants with CVD are men and women aged 40 years and older with a previous diagnosis of CVD (history of prior acute coronary syndrome, revascularization, or exertion angina). Main household shoppers (this may be the same person) must be 18 years and older, own or have access to a smartphone (iPhone or Android), and shop at the supermarket for household food at least once per week, spending $25 or more per household member.

Participants with CVD must not have suffered a cardiac event in the past three months, been diagnosed with heart failure or severe valve disease, be on a physician supervised diet or unwilling to make dietary changes, or be taking any medication that may lead to hyponatraemia or fluid retention (frusemide, regular non-steroidal anti-inflammatory (NSAID) use (excluding aspirin), or regular prednisone use). A cardiac event is defined as hospitalization for a heart attack, coronary artery revascularization, stroke, or heart failure. Main household shoppers must not currently use the FoodSwitch smartphone app or plan to use it during the next six weeks. All participants must not be planning on going away from home (vacation or otherwise) for more than three days in the next six weeks.

### Recruitment

Potentially eligible participants are invited to take part in the study via advertisements in supermarkets, hospital waiting rooms, healthcare organization newsletters, community newspapers, and other public spaces, and through social media (Facebook and Twitter). Research assistants also identify potential participants using an existing University of Auckland database comprising people with diagnosed CVD who previously agreed to be contacted for future research, a market research panel, and through cardiac rehabilitation clinics. Research assistants provide all potential participants with a summary of the trial over the phone to determine their interest in taking part. Those agreeing to participate are screened for eligibility and sent a study pack including a participant information sheet and consent form. Interested and eligible participants are allocated a unique study registration number including a household code (001 to 300), a number to indicate whether there are one or two people participating in the household (1 or 2), and a code to indicate whether they are the primary participant with CVD (1), or the secondary participant (main household shopper; 2). Participants with CVD are scheduled for a baseline assessment. Main household shopper participants who do not have CVD are sent a link in an email to complete an on-line questionnaire.

### Sample size

The target sample size of 300 participants with CVD (150 per group) will provide 80% power at 5% level of significance (two-sided) to detect a treatment difference of 0.07 g/MJ (~10%) of salt in household food purchases, between the two groups at follow up (average over weeks five and six) assuming a standard deviation of 0.22 g/MJ. The target sample size was estimated using data on baseline purchases of salt (mean (SD), 285 (88) mg/MJ) made by participants in a previous supermarket intervention trial (n = 1,104) in New Zealand [24] and estimated intervention effects from the Dietary Approaches to Stop Hypertension study [25].

### Ethical approval

Ethical approval was obtained from The University of Auckland Human Participants Ethics Committee on 16^th^ December 2013 (reference number 010998).

### Intervention

The intervention group receives the SaltSwitch smartphone app for four-weeks. SaltSwitch enables the user to scan the barcode of packaged foods and beverages using the phones camera and receive an immediate interpretive, traffic light nutrition label on screen, along with a list of healthier lower-salt alternatives to ‘switch’ to (Figure 1).

The New Zealand SaltSwitch app is underpinned by a database of ~13,000 barcodes and nutritional information for packaged foods and non-alcoholic beverages for sale in supermarkets and convenience stores [26]. Data are collected annually by fieldworkers [26]. SaltSwitch also incorporates crowd-sourcing; when a user scans the barcode of a product not already in the database, they are prompted to take three photographs (one each for the front of the pack, the nutrition information panel, and the ingredient list). Photographs are then sent to the research team and new products are subsequently added to the app.

The traffic light labels are determined using the United Kingdom’s Guidance for creating a front of pack nutrition label for pre-packaged foods [27], and healthier options are determined using the Australia New Zealand Food Standards Agency Nutrient Profiling Scoring Calculator (NPSC), a nutrient profiling model (scoring system to rank foods) used to determine whether foods are eligible to carry nutrition and health claims in Australia and New Zealand [20]. The NPSC system allocates a score to food products by balancing positive nutrients such as fibre and protein with negative nutrients including salt and saturated fat.

Main household shoppers in the intervention group are sent a link to download the SaltSwitch app to their smartphone, and are provided with a telephone tutorial. Intervention shoppers receive a reminder text message each week and are encouraged to use the app when shopping for household food and beverages.

### Control

Those randomised to the control group continue to shop as normal, and are able to access cardiac rehabilitation services as per usual care for people with CVD in New Zealand. Participants in the control group are advised on enrolment that they will be offered SaltSwitch on completion of the trial.

### Primary outcome

The primary outcome is the salt content of household food purchases (g/MJ) at the end of intervention (weeks five and six).

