### Secondary outcomes

Saturated fat (g/MJ), energy content (kJ/MJ), and expenditure ($/MJ) on household food purchases will be assessed at the end of intervention (weeks five and six). Systolic blood pressure, ambulatory blood pressure (sub-study 1; n ~ 40), and urinary sodium of the household member with CVD, and use and acceptability of the SaltSwitch app (main household shopper) will be assessed at baseline (week 0) and end of intervention (week 6). With the exception of ambulatory blood pressure, all outcomes will be assessed over the longer-term, at weeks 11 and 12, in a sub-group of ~20 people with CVD (and their main household shopper where applicable) who remain enrolled in the study (sub-study 2). Serious adverse events (SAEs) will be recorded for the duration of the study.

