Weight, height, blood pressure and urine samples are collected using standard procedures. Weight is measured on a Salter scale to the nearest 0.1 kg and height is measured on a stadiometer to the nearest cm. Blood pressure of participants with CVD (mean of three readings taken at least 3 minutes apart) is assessed seated, after 10 minutes rest, using an OMRON automatic blood pressure monitor. Participants with an average blood pressure >160/90 mmHg, with an average systolic blood pressure <90 mm/Hg, or who report dizziness when going from sitting to standing, are advised to discuss this with their General Practitioner. Prior to commencement of the trial and annually thereafter, the Salter scales and OMRON automatic blood pressure monitor were serviced and verified according to manufacturer recommendations.

Participants in sub-study 1 assessing ambulatory blood pressure are provided a calibrated Mobil-O-Graph Ambulatory 24-hour Blood Pressure Monitoring System and instructions. Sub study 1 participants are instructed to wear the monitor for one 24-hour period within the following five days and keep a diary to record events such as bed and wake-up times. Ambulatory blood pressure will be analysed using programming software for the Mobil-O-Graph.

Twenty-four hour urinary sodium excretion is considered the gold standard for measurement of sodium intake [23]. However, 24-hour urine collections carry a high participant burden and are prone to under- and over-collection and low response rates [28]. In contrast, single urinary sodium collections carry a low participant burden and may provide a reasonable estimate of the sodium intake of a group [29]. Mid-stream urine samples are collected in standard clinical urine lab containers. Five millilitres of the urine sample is transferred to a labelled, 10 mL freestanding tube and stored in a secure −4°C freezer. Frozen samples are couriered in batches to a certified laboratory and converted to predicted 24-hour urinary sodium excretion using the INTERSALT formula [30].

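### The primary outcome is salt per MJ: if purchased energy falls as the trial hypothesises, it understates a real cut in salt, and no listed purchase outcome would show this

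*Protocol article*

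**What the plan says.** Under Primary outcome: "The primary outcome is the salt content of household food purchases (g/MJ) at the end of intervention (weeks five and six". The hypothesis in the closing paragraph of the Background names no denominator. It says that "four weeks’ intervention with SaltSwitch will reduce the salt content of household food purchases compared with control", and the primary aim under Aims likewise refers to salt content without a unit.

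The same Background paragraph gives a secondary hypothesis that the app "will reduce the saturated fat and energy content of household food purchases". The trial therefore expects the denominator of its primary outcome to change after randomisation.

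Under Secondary outcomes: "Saturated fat (g/MJ), energy content (kJ/MJ), and expenditure ($/MJ) on household food purchases will be assessed". Every nutrient and spending outcome taken from till receipts is thus expressed per MJ, energy included.

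Outside the receipts, Measurement of study outcomes provides for a single urine sample from the participant with CVD, "converted to predicted 24-hour urinary sodium excretion using the INTERSALT formula".

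**The concern.** A ratio can move because its numerator moves or because its denominator does. If the app lowers salt and energy in the same proportion, salt per MJ does not change, although the household has bought less salt. The two hypotheses therefore work against each other on the primary endpoint: the larger the energy effect, the smaller the visible salt effect.

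This could be checked if the plan reported how much energy was bought. As listed, it does not. If the MJ in kJ/MJ is the purchased energy, the outcome equals 1,000 for every household in both arms. No purchase outcome gives absolute salt. The planned ANCOVA adjusts for the baseline outcome, ethnicity, age and gender, none of which captures energy bought at follow-up.

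At stake is the reading of the main result. A null g/MJ result could mean that the app did nothing, or that households bought less salt and less energy together.

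**Working it through.** **Inputs.** From Sample size: "The target sample size of 300 participants with CVD (150 per group"); "80% power at 5% level of significance (two-sided"); a difference of 0.07 g/MJ, described as roughly 10%; SD 0.22 g/MJ; and source data of 285 (88) mg/MJ. The control mean in g/MJ is not stated. Multiplying the source figures by 2.5 gives 0.7125 (0.22) g/MJ, which matches the stated SD and makes 0.07 about 10% (0.07/0.7125 = 9.8%). I take 0.7125 g/MJ as the control mean on that basis; it is an inference.

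**The plan's own figure.** Standard error of the difference = 0.22 × √(2/150) = 0.0254. Power = Φ(difference/0.0254 − 1.96).
- Difference 0.07: power 0.787.
- Difference 0.07125 (10% of 0.7125): power 0.801, needing exactly 150 per arm.

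The stated 80% is reproduced.

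**Effect of a moving denominator.** If salt falls by a fraction s and energy by a fraction e, the intervention mean is 0.7125 × (1 − s)/(1 − e). The documents give no value for e, so the values below are assumptions. The SD is held at 0.22, and power is for a significant result in the favourable direction.

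True salt reduction of 10%:

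| Energy fall (assumed) | Intervention mean, g/MJ | Difference, g/MJ | Change in ratio | Power |
|---|---|---|---|---|
| 0% | 0.6412 | 0.0713 | −10.0% | 80% |
| 2% | 0.6543 | 0.0582 | −8.2% | 63% |
| 5% | 0.6750 | 0.0375 | −5.3% | 31% |
| 10% | 0.7125 | 0 | 0% | 2.5% |
| 15% | 0.7544 | −0.0419 | +5.9% | below 0.1% |

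In the 10% row nothing is left to detect. The figure is the type I error rate: 2.5% in the favourable direction, 5% counting both.

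**The same point in reverse.** The absolute salt fall needed to keep a 0.07 g/MJ difference is 1 − (1 − e)(1 − 0.07/0.7125). For energy falls of 0, 2, 5 and 10% this is 9.8%, 11.6%, 14.3% and 18.8%.

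**The opposite direction.** With salt unchanged, an apparent reduction of 0.07 g/MJ needs energy to rise by 1/(1 − 0.07/0.7125) − 1 = 10.9%. With salt unchanged and energy down 5%, the ratio rises 5.3%, which would look like harm.

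**The case against.** The strongest reply is that density is the right measure here. The trial is about choosing lower-salt foods, and the app works by substitution, designed so that "healthier alternatives are always lower in salt than the product scanned". Salt per MJ describes the composition of the basket. It does not depend on household size or, if the mix is similar, on the share of receipts returned. With self-returned receipts, unblinded participants and no imputation, that robustness matters. This stands, and it is why g/MJ should remain primary.

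It is also fair that the size of any energy change is unknown and that baseline adjustment may reduce the residual SD. More precision would raise power wherever a difference in the ratio remains, but it would not restore the part of the effect that a falling denominator removes.

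Three stronger readings are tempting, and the documents do not support them.
- A reader might infer that the ratio could also mimic a salt reduction. A falling denominator can only push g/MJ up. Mimicry needs energy to rise, contrary to the stated hypothesis.
- A reader might infer that no absolute sodium measure is planned. Predicted 24-hour urinary sodium is a secondary outcome and does not depend on purchased energy. However, it comes from one spot sample in one household member and says nothing about how much energy was bought.
- A reader might worry that items with salt but almost no energy, such as table salt, would swamp a household's value. The documents give no figures on this, the source SD may already include such purchases, and rules for items and outliers ordinarily belong in the statistical analysis plan, which is not shown.

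**Conclusion.** The concern holds in a limited form. Using g/MJ is not an error. The weakness is that the hypothesis and aim are worded as salt content, the outcome measures salt density, the trial itself predicts a fall in the denominator, and the listed purchase outcomes cannot show whether that fall occurred.

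For a true 10% cut in salt, an energy fall of only 5% takes power from 80% to about 31%, and a 10% fall removes the difference altogether. These figures rest on assumed energy changes, an inferred control mean of 0.7125 g/MJ, a constant SD and a normal approximation. The direction of the distortion needs none of these assumptions: if purchased energy falls, the proportional fall in g/MJ is smaller than the proportional fall in salt.

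The change is worth making because it is cheap and makes either a null or a positive primary result interpretable.

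**What to change.** Keep g/MJ as the primary outcome and state in the hypothesis, aim and outcome definition that the target is salt density. Replace the kJ/MJ outcome with energy purchased in MJ per household member per day, and add salt purchased in g per household member per day. Derive both from the same weeks five and six receipts, analyse them with the same ANCOVA, and label them supportive. Report them beside the primary result together with urinary sodium.

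The cost is small: no new data collection, since receipts are already gathered and household size is needed for the $25-per-member spending rule. The drawback is that per-person amounts are noisier and can be biased if unreturned receipts differ between the unblinded arms. They should therefore inform the interpretation of the primary result and not be a condition for declaring it positive.
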